# QUALITY ASSURANCE OF SURGERY AND FERTILITY TREATMENT

PARTICIPATING CENTERS

All participating surgical centers have been selected by the National Board of Health and Welfare following an application process to perform highly specialized advanced endometriosis surgery at a national level. A quality assessment form including institutional experience with endometriosis surgery and ART, annual volume of benign gynecological complex cases must be completed. Moreover, surgical variables (e.g. operation time, blood loss) and complications within 30 days after surgery according to Clavien Dindo (22) must be reported . Furthermore, the infrastructure to participate in the trial must be satisfactory. In addition, the institution’s ability to perform staging of endometriosis is considered. All ART-clinics authorized to provide publicly funded fertility care report their results continuously to the National Quality Registry for Assisted Reproduction (Q-IVF).

During the study, it is at the discretion of the coordinating investigators and Trial steering committee to close centers with a higher-than-average rate of postoperative major

complications or poor quality of surgery or ART, from further accrual, temporarily or irrevocably after consultation with the Data Safety Monitoring Board.

PARTICIPATING SURGEONS

All included surgeons must be approved by the coordination investigators or/and trial steering committee ensuring adherence to protocol. In the site identification and quality assessment form the participating surgeons experience and annual caseload will be reported for review. It is at the discretion of the coordinating investigators or/and steering committee to select or deselect individual surgeons from participating in the trial. Only surgeons stated in the Quality assessment form are allowed being lead surgeons, amendments during the trial can be made.

Robot-assisted laparoscopic or traditional laparoscopic endometriosis surgery

All included surgeons must have a previous experience of at least 20 advanced endometriosis surgeries.

# PATIENT REPORTED OUTCOMES (PROMS)

When evaluating quality of life among women with endometriosis many different scales have been used, mostly of generic character that are not specific to the disease. One of these is 30-item Endometriosis Health Profile (EHP30), a scale that perform well in clinical practice in the routine evaluation of Health-Related Quality of life (HRQoL) The use of EHP30 is recommended by the National Board and Welfare in Sweden, the ASRM and ESHRE (40). Using EHP-30, a small study has shown an improvement in HRQoL in the follow-up after endometriosis surgery, an effect that may last for up to 6.8 years (41). Two recent studies show postoperative improvement in HQQoL measured by EHP-30 10 weeks and 3 months after surgery, respectively (42, 43). Especially women with deep endometriosis (DE) showed a more significant benefit from surgery (43). However, HRQoL can also be affected by infertility, and in this trial, infertility treatment will be delayed, thus, HRQoL is an important measurement.

POINTS OF ASSESSMENT

Baseline assessment will be obtained after randomization and maximum 1 month prior to surgery or start of first ART cycle

Thereafter assessment will be done prospectively at:

- 2 months after surgery (for the group randomized to first line surgery)
- 1:st oocyte pick up (for both randomization groups)
- 2 months after 1:st oocyte pick up
- 2:nd oocyte pick up
- 2 months after 2:nd oocyte pick up
- 3:rd oocyte pick up
- 2 months after 3:rd oocyte pick up
- Visit, phone call or questionnaire 3 years after randomization.

Compliance with completing the questionnaires will be investigated at each time point to

evaluate the procedure for data collection and the feasibility of the questionnaires.

INSTRUMENTS

The core questionnaire in EHP -30 includes 30 questions in 5 health-related areas: pain, control and powerlessness, emotional well-being, social support, and self-image. In addition, there are six supplementary modules covering work, relationship with child/children, sexual relationship, feelings about the medical profession, feelings about treatment and feelings about infertility.

The Numeric Rating Scale (NRS) is a frequently utilized pain assessment tool commonly employed in postoperative care. It allows for the momentary evaluation of pain on a scale from 0 to 10, with 0 representing "no pain" and 10 indicating "the worst pain imaginable”.

EQ-5D is a standardized non-disease specific instrument for describing and

valuing HRQoL, developed by the EuroQoL group. It includes five dimensions (mobility,

self-care, usual activities, pain/discomfort and anxiety/depression) with three levels of

responses each (no problems, some problems or extreme problems). The EQ-5D also

comprises a 20cm visual analogue scale (VAS) ranging from 0 (worst imaginable

state) to 100 (best imaginable health state) on which the respondent rates the current health.

The index-based score is interpreted along a continuum where 1 represents best possible health and 0 represents dead. Some health states are given a figure below zero (worse than

death).

PROCEDURE

The first questionnaire kit (EHP-30, NRS and EQ-5D) will be administered after the patient is informed about their randomized study arm. This timing has been chosen to ensure that the baseline assessment is collected a similar length of time before the planned intervention in both study arms, since the date of surgery or ART treatment can only be scheduled after randomization. This approach minimizes bias related to varying waiting times between randomization and treatment initiation., The patient will receive both oral and written information about the Health-Related Quality of Life (HRQoL) assessment. Subsequent questionnaires will be collected during clinic visits, electronically, or via conventional mail at predefined time-points (please see above). Treating physicians will not have access to the HRQoL study forms. Completed questionnaires will always be considered source documents and must be filed accordingly.

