# STUDY FLOW CHART

# SCHEDULE OF EVENTS TABLE

| Procedures | **Baseline** | **Enrolment** | **1 month prior to surgery or start of first ART cycle^1^** | **Surgery^2^** | **2 months postoperative visit^2^** | **1:st oocyte retrieval** | **2 months after 1:st oocyte retrieval** | **2:nd oocyte retrieval** | **2 months after 2:nd oocyte retrieval** | **3:rd oocyte retrieval** | **2 months after 3:rd oocyte retrieval** | **Visit, phone call or questionnaire 3 years after first treatment (surgery or first ART cykle)** |
| --- | --- | --- | --- | --- | --- | --- | --- | --- | --- | --- | --- | --- |
| **Informed consent oral and written** | x |  |  |  |  |  |  |  |  |  |  |  |
| **Demographics** |  |  | x |  |  |  |  |  |  |  |  |  |
| **Record ultrasound and/or MRI staging according to AAGL and #ENZIAN staging system** | x |  |  |  |  |  |  |  |  |  |  |  |
| **Randomization** |  | x |  |  |  |  |  |  |  |  |  |  |
| **Record surgical procedure according to AAGL and #ENZIAN staging system** |  |  |  | x |  |  |  |  |  |  |  |  |
| **Record intraoperative complications^3^** |  |  |  | x |  |  |  |  |  |  |  |  |
| **Hospital stay** |  |  |  | x |  |  |  |  |  |  |  |  |
| **Record 8 weeks postoperative complications^4^** |  |  |  |  | x |  |  |  |  |  |  |  |
| **EHP-30, EQ5D and NRS scale^5^** |  |  | x |  | x | x | x | x | x | x | x | x |
| **Primary outcome (CLBR)** |  |  |  |  |  |  |  |  |  |  |  | x |
| **Secondary outcome/IVF cycle^6^** |  |  |  |  |  |  | x | x | x | x | x | x |

^1^ start of FSH injections ^2^only first line surgery group ^3^According to Classic ^4^According to Clavien Dindo ^5^Endometriosis Health Profile and Numeric Rating Scale ^6^LBR, PR, number of oocytes retrieved, fertilization grade, number of blastocysts

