In Sweden in 2023, 9.9% of patients undergoing surgery for endometriosis within the framework of national highly specialized care experienced mild complications Clavien Dindo 1-2 (e.g. infection and hematoma at the surgical site), and 3.3% experienced serious complications Clavien Dindo 3 (e.g. bowel leakage, unexpected bladder injury, ureteral injury, or intra-abdominal bleeding requiring reoperation) (38). Serious complications may, in rare cases, necessitate further surgical interventions. The risk of complications varies slightly depending on the location of the endometriosis (38).

Patients undergoing surgery will need to delay ART treatment by two to three months in order to fully recover.

FERTILITY TREATMENT WITH ART

ART treatments will be carried out at Swedish reproductive units authorized to provide publicly funded fertility care. The majority of treatments are expected to take place at the university-affiliated reproductive clinics in Stockholm, Gothenburg, Skåne, and Uppsala. However, for participants residing in other regions of Sweden, undergoing treatment locally offers a significant advantage by reducing the logistical and emotional burden of long-distance travel to these central clinics. To ensure equitable access and minimize patient stress, regional ART centers will be considered when appropriate.

One IVF/ICSI-cycle is defined as the transfer of all the embryos created via that particular oocyte pick-up until pregnancy confirmation or until the failure of the last embryo transfer. In case of a cancelled cycle prior to oocyte pick-up it will not be counted. The duration of one IVF-cycle depends on the number of embryo transfers and typically ranges between two and nine months.

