**Quality of Life and Health Status Measures:**

**EHP-30 (continuous, 0–100 scale):**
Analyzed using a linear mixed-effects model (LMM) with random intercepts for participants. Fixed effects will include treatment group, time, and the treatment×time interaction, adjusting for prespecified covariates (age, BMI, AMH, center).

**EQ-5D (continuous index 0–1):**Analyzed using the same LMM framework as EHP-30 (random intercepts, treatment, time, treatment×time, prespecified covariates).

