**Additional analysis**

– Exploratory subgroup analyses will not be adjusted for multiplicity.

– Safety outcomes will be summarized descriptively by treatment group (frequency, severity, relation to treatment).
– All available data will be used, including outliers.
– Missing outcome data will be handled under the missing-at-random assumption via maximum likelihood in mixed models; for regression models requiring complete covariates, complete-case analysis will be applied.

Covariates

Primary and secondary outcomes will be adjusted for prespecified covariates (age, BMI, AMH, ART type, center), chosen based on clinical relevance and prior evidence.

POWER CALCULATION AND SAMPLE SIZE

The sample size calculation was based on a two-sample comparison of proportions with a two-sided α=0.05 and 80% power. Based on observational data (18, 19), the cumulative live birth rate (CLBR) after three IVF cycles was assumed to be 55% in the ART-only group and 71% in the surgery+ART group (relative risk ≈1.29). This yields a required sample size of 142 participants per arm (284 total). Allowing for 20% attrition, the planned total sample size is 350 participants.

The necessary sample size for this study is estimated to 323 patients to accommodate a statistical analysis method. This estimation uses the 'pwr' package in R, specifically employing the power.prop.test method, which is designed to compare two proportions. This method is more aligned with contemporary statistical practices and provides a clear, transparent methodology for determining the required sample size based on expected success rates.

This means inclusion of 29 patients from/each center/year and 15 surgeries/year. In a Swedish study published in 2022 the prevalence of endometriosis in patients referred for ART-treatment was 21.8% and 17.2% of women had DE (14). In 2021 almost 10 500 IVF cycles were performed in Sweden, while more than 5 500 of those were first-time IVF/ICSI with autologous gametes ((46) Figure 22).

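### Quality of life and pain are to be compared between arms at pick-up visits, which fall at different times in the two arms and, from the second pick-up on, mainly in women whose earlier cycles failed

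*Protocol*

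**What the plan says.** Under Study objectives (Secondary objectives), the protocol asks whether surgery first gives better EHP-30 and NRS results than ART first at oocyte retrieval, two months after ART and the three-year visit.

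Patient reported outcomes (Points of assessment) and the Schedule of events table give nine times:

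- baseline;
- "2 months after surgery (for the group randomized to first line surgery";
- the "1:st oocyte pick up (for both randomization groups";
- the second and third pick-ups;
- two months after each pick-up, the last being "2 months after 3:rd oocyte pick up";
- three years.

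The two sections anchor the last time differently: "Visit, phone call or questionnaire 3 years after randomization" in the first, "Visit, phone call or questionnaire 3 years after first treatment (surgery or first ART cykle" in the second.

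For EHP-30 the mixed model is described thus: "Fixed effects will include treatment group, time, and the treatment×time interaction". EQ-5D uses the same framework, and NRS an ordinal version with the same fixed effects. How time enters is not stated. Under Additional analysis: "Missing outcome data will be handled under the missing-at-random assumption via maximum likelihood in mixed models".

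Study treatment adds: "Patients undergoing surgery will need to delay ART treatment by two to three months in order to fully recover". Under Fertility treatment with ART, a cycle runs until pregnancy is confirmed or the last transfer fails, and frozen embryos are planned to be used before any new stimulation. Health economics derives QALYs from the same EQ-5D data.

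**The concern.** A randomised comparison needs the same women, or a fair sample of them, measured at comparable times in each arm. A pick-up visit does not provide this.

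First, the same visit falls later after first treatment in the surgery arm. That interval matters, because the protocol itself cites improved EHP-30 scores 10 weeks and 3 months after surgery. The Procedure section aligns the baseline with treatment start to limit timing bias, but nothing does so for later visits.

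Second, a second or third pick-up normally happens only when earlier cycles have failed. The women seen there are selected on the primary outcome, and if surgery works as hypothesised the selection is stronger in the surgery arm.

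At stake are the quality-of-life and pain conclusions, and the EQ-5D profile behind the cost-utility analysis.

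**Working it through.** **Visit count.** Nine times: one is tied to surgery (surgery arm only), six to pick-ups, and two (baseline and three years) are due in every woman.

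**Reproducing the protocol's figure.** The patient-reported outcomes have no sample-size figure, so I checked the one that supplies the live-birth rates. With 55% against 71%, two-sided 0.05, 80% power and pooled variance:

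n = [1.96·√(2·0.63·0.37) + 0.8416·√(0.55·0.45 + 0.71·0.29)]² / 0.16² = (1.338 + 0.567)² / 0.0256 ≈ 141.8, so 142 per arm and 284 in total, as stated. Dividing 284 by 0.8 gives 355; the protocol plans 350, or 175 per arm.

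**Timing.** Inputs: a 2–3 month delay after surgery and cycles of 2–9 months (both from Study treatment), plus an assumed 0.5 month from stimulation start to pick-up. Months after first treatment:

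| | ART arm | Surgery arm |
|---|---|---|
| First pick-up | 0.5 | 2 + 0.5 = 2.5 to 3 + 0.5 = 3.5 |
| Third pick-up | 0.5 + 2·2 = 4.5 to 0.5 + 2·9 = 18.5 | 2.5 + 4 = 6.5 to 3.5 + 18 = 21.5 |

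The offset between arms is 2–3 months. Cycle length spreads the third pick-up over 14 months within an arm.

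**Selection.** Assume that success accrues evenly over three cycles and that nobody stops for other reasons. The share not succeeding per cycle is q = (1 − CLBR)^(1/3).

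- ART: q = 0.45^(1/3) = 0.766; q² = 0.587.
- Surgery: q = 0.29^(1/3) = 0.662; q² = 0.438.

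| Reaching | ART (of 175) | Surgery (of 175) |
|---|---|---|
| Pick-up 1 | 100% (175) | 100% (175) |
| Pick-up 2 | 77% (134) | 66% (116) |
| Pick-up 3 | 59% (103) | 44% (77) |

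The surgery column excludes spontaneous conception before the first pick-up. The protocol calls this frequent after surgery for deep endometriosis but gives no rate. If a share s conceives this way and the total stays at 71%, then q = (0.29/(1 − s))^(1/3). For s = 20% (assumed), the surgery arm has 80%, 57% and 41% at the three pick-ups. Over s = 0–30% the ranges are 100–70%, 66–52% and 44–39%.

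**Illustrative size in EHP-30 points.** A small simulation used no treatment effect, SD 20 and no spontaneous conception, with women of better quality of life conceiving sooner (all assumed).

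- Raw visit means, correlation 0.2–0.6: the surgery arm looks worse by 0.6–1.9 points at the second pick-up and 0.9–2.9 at the third.
- Random-intercept mixed model, correlation 0.4: about 0.2–0.4 points, with a simulation standard error of about 0.2.
- Change after conception, not seen at pick-up visits: if conception improved the score by 5–15 points (assumed), the missed difference over all randomised women is that gain times the difference in success. At the second pick-up, (0.766 − 0.662) × 5 to 15 = 0.5–1.6 points; at the third, (0.587 − 0.438) × 5 to 15 = 0.7–2.2 points.

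**The case against.** The protocol does not say that time means a visit label, and an analysis plan may define it otherwise. A reader might infer that the model must estimate a treatment effect at the post-surgery visit, which exists in one arm only. The text does not support that: the visit is not among the objective's named comparison points, and it could be left out of the contrast. The definition of the outcome also mentions two months after ART or surgery, which might pair that visit with an ART visit, although the schedule lists it separately. This part of the objection stands. It does not dispose of the point, because the objective itself names retrieval and two months after ART as comparison points, and no coding of time changes who is seen there.

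A reader might also infer that missing-at-random handling fails outright and the results are badly biased. The check does not show that: the mixed model leaves little of the selection on stable quality of life. What remains is quality of life after conception.

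Nor can it be said that women who conceive spontaneously, or succeed in an early cycle, never reach a later pick-up. Some miscarry and start or resume ART, and visits two months after a pick-up can include newly pregnant women.

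Finally, these endpoints are declared supportive and exploratory, and sensitivity analyses for missing data and alternative models are promised. This limits the severity but does not make the pick-up contrasts interpretable.

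**Conclusion.** The point holds and merits a change, though it does not touch the primary analysis. Between-arm contrasts at pick-up visits mix treatment effect with a 2–3 month difference in elapsed time and with arm-dependent selection: about 77% against 66% at the second pick-up and 59% against 44% at the third. These shares rest on the protocol's 55% and 71%, the even-accrual assumption and no spontaneous conception. The effects in EHP-30 points are modest and depend on assumed inputs.

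The three-year contrast is largely free of the problem, because that assessment does not depend on failing to conceive. Its anchor is contradictory, however. Study treatment aims for three months between randomisation and first treatment and prefers no more than six, so the two readings can differ by that much.

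It would be wrong to conclude that redefining time cures everything. It aligns the clock but adds no measurements. A woman who conceives early has no planned EQ-5D value between about two months after her last pick-up (or after surgery) and year three.

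**What to change.** In the secondary objectives and the EHP-30, EQ-5D and NRS model descriptions:

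1. Name the three-year assessment as the randomised between-arm contrast.
2. Reconcile its anchor between Points of assessment and the Schedule of events table.
3. Define time in the models as time since that common anchor.
4. Report pick-up scores descriptively by cycle, and the two-month post-surgery score within the surgery arm only.
5. State as a limitation of the QALY analysis that EQ-5D is unmeasured after early conception until year three, and that re-analysis cannot fill the gap.

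The cost is a change of wording, including to a stated secondary objective; no extra data collection is required. The downside is that pick-up comparisons in an exploratory objective lose their status as randomised contrasts. Closing the EQ-5D gap itself would need added questionnaire waves at fixed times, a separate decision for the sponsor.

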# STUDY DESIGN

An open label randomized controlled trial.

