# STUDY TREATMENT

Time from randomization to first treatment (surgery or first ART cycle) should be minimized with a goal of three months and should preferably not exceed six months. Complications due to treatments (IVF or surgery) will be register in the eCRF and treated according to clinical routine at each hospital.

EXPERIMENTAL TREATMENT

First line endometriosis surgery followed by ART such as IVF or ICSI.

STANDARD/CONTROL TREATMENT

First line ART such as IVF or ICSI.

SURGICAL PROCEDURE

Surgery will be performed at one of four nationally specialized centers in advanced endometriosis surgery (Södersjukhuset Stockholm, Sahlgrenska University Hospital Göteborg, Skånes University Hospital, Malmö/Lund, Uppsala University Hospital). Intraoperative AAGL endometriosis staging, #ENZIAN classification and Endometriosis Fertility Index (EFI) (31) will be recorded in the study protocol. Surgery will be conducted according to the ESHRE recommendations of surgery in endometriomas and deep endometriosis (32, 33). Surgery should be multidisciplinary when needed (colorectal surgeons and urologists). The goal of the procedure is to remove as many endometriotic lesions as possible while also minimizing negative impact on organ function, since endometriosis is a benign disease. Rectal endometriosis will be removed with rectal shaving, discoid or segmental resection depending on the size and placement of the lesion in the rectal wall. Laparoscopic cyst enucleation is considered the "golden standard" as it is associated with a low recurrence rate, significant pain relief, and increased chances of spontaneous conception (34). In cases where ovarian reserve is already diminished, more gentle methods such as ablation therapy with CO2 Laser/Plasma Jet or sclerotherapy could be employed (35-37). These methods can also be used in combination with conventional surgical cyst enucleation. The choice of surgical technique should be tailored to the individual patient's needs.

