**NRS pain (ordinal: mild 1–3, moderate 4–6, severe 7–10):**
Analyzed using a generalized linear mixed model (GLMM) with cumulative logit link (ordinal logistic regression), including random intercepts for participants, fixed effects for treatment, time, and treatment×time, and prespecified covariates (age, BMI, AMH, center).

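### The only baseline EHP-30, NRS and EQ-5D is collected after the woman knows her arm, so comparisons that use it as reference may carry an allocation effect

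*Protocol*

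**What the plan says.** The Study Design section describes "An open label randomized controlled trial". Under Patient Reported Outcomes, Points of Assessment, the plan is: "Baseline assessment will be obtained after randomization and maximum 1 month prior to surgery or start of first ART cycle". The Procedure paragraph adds that the first kit (EHP-30, NRS and EQ-5D) "will be administered after the patient is informed about their randomized study arm".

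The Schedule of Events agrees. Consent and imaging stand in the Baseline column and randomisation in the Enrolment column. The questionnaires first appear in the next column, one month before surgery or the first ART cycle. None is listed earlier.

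The timing is deliberate. The Procedure paragraph explains that the "baseline assessment is collected a similar length of time before the planned intervention in both study arms", and claims: "This approach minimizes bias related to varying waiting times between randomization and treatment initiation".

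Under Study Treatment, the time from randomisation to first treatment "should be minimized with a goal of three months and should preferably not exceed six months".

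For EHP-30, and by reference for EQ-5D, the statistical section specifies a linear mixed model: "Fixed effects will include treatment group, time, and the treatment×time interaction". For NRS it specifies an ordinal mixed model with "fixed effects for treatment, time, and treatment×time". The Health Economics section bases its cost-utility analysis on changes in health status and quality of life.

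**The concern.** A baseline is useful as a reference because randomisation makes its expected between-arm difference zero. That guarantee is lost once the reading is taken after the arm is disclosed.

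The instruments here are open to such an influence. EHP-30 covers control and powerlessness, emotional well-being and, in its modules, feelings about treatment and infertility. EQ-5D includes anxiety and depression. The protocol itself notes that quality of life can be affected by infertility and that fertility treatment will be delayed in this trial. Women in the surgery-first arm learn of that delay before they answer the first kit.

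The stated reason covers equal lead time before treatment. It justifies a pre-treatment reading, but it does not address a response influenced by knowing the arm, and it gives no reason to omit a reading before allocation. At stake is the credibility of quality-of-life, pain and QALY results that are expressed relative to the first kit.

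**Working it through.** The protocol gives no SD, correlation or expected difference for these instruments, so there is no stated figure to reproduce. The arithmetic below is an illustration for EHP-30 on assumed inputs.

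**Timing.** With a goal of three months and a preferred limit of six, and the kit in the last month before treatment, baseline may fall about 3 − 1 = 2 to 6 − 1 = 5 months after randomisation. The Randomization section also has eligibility criteria entered in REDCap one month before first treatment, which could mean a shorter gap. Either way, the kit follows disclosure of the arm.

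**Inputs.**
- Analysed per arm: 350 × 0.8 / 2 = 140 (planned total less the protocol's 20% attrition).
- SD 20-25 on the 0-100 scale: assumed.
- Baseline-to-follow-up correlation ρ 0.5-0.7: assumed.
- Shift δ in one arm at the first kit, absent at follow-up, with no true follow-up difference: assumed.

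**Pure change contrast.** The bias is −δ. SE = SD × √(2(1 − ρ)) × √(2/140).
- Smallest: 20 × √0.6 × 0.1195 = 1.85.
- Largest: 25 × √1 × 0.1195 = 2.99.

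The false-positive rate is Φ(−1.96 + δ/SE) + Φ(−1.96 − δ/SE):

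| δ (points) | False-positive rate (nominal 5%) |
|---|---|
| 1 | 6-8% |
| 3 | 17-37% |
| 5 | 39-77% |

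**Comparison of analyses.** A simulation used SD 20, ρ = 0.5, 140 per arm and 1,500 replicates:

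| δ | Bias, change | Bias, ANCOVA | Bias, follow-up level | False positives, change | False positives, ANCOVA |
|---|---|---|---|---|---|
| 0 | 0.0 | 0.0 | 0.0 | 5.0% | 5.3% |
| 2 | −2.1 | −1.1 | −0.1 | 14% | 8% |
| 4 | −4.1 | −2.0 | 0.1 | 41% | 18% |
| 6 | −5.9 | −2.9 | 0.0 | 68% | 28% |

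ANCOVA carries −ρδ, hence about half the shift at ρ = 0.5; at ρ = 0.7 it would carry 70%. The between-arm level at follow-up does not use the first kit and stays unbiased.

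**Mixed model.** One large simulated data set (2,000 per arm, δ = 4, no true follow-up difference) was fitted with treatment, time and treatment×time. It gave a treatment effect at baseline of 3.90 and an interaction of −3.73. Their sum, 3.90 − 3.73 = 0.17, is the follow-up level difference and is close to the true zero. The interaction absorbs the shift; the level contrast does not.

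**Can the shift be seen?** The SE of the between-arm difference at the first kit is SD × √(2/140) = 2.39-2.99. By the same formula, a 5-point shift would be significant at 5% in about 39-55% of trials. A 3-point shift would be significant in about 17-24%.

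**The case against.** The strongest reply is that the protocol names no change score. It does not say whether the first kit is a time level in the models or which contrast will be reported; that may be settled in an analysis plan not at hand. The secondary objective can be read as comparing the arms at oocyte retrieval, two months after ART and three years, and the same models can estimate those levels without using the first kit as reference. This stands, and it limits the point to baseline-referenced contrasts and the QALY changes.

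The timing is also a reasoned choice, aligned with the protocol's definition of trial start as first treatment. That stands as a reason to keep the pre-treatment kit, but not as a reason to have no other.

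Four stronger readings are tempting, and the documents do not support them:
- *Every follow-up comparison is biased.* Between-arm levels at follow-up are not.
- *The shift cannot be detected or corrected.* It would appear as a baseline imbalance, though with limited power and not reliably separable from chance. Level contrasts avoid it.
- *The false-positive risk is 39-77%.* That figure needs a 5-point shift, assumed SDs and correlations, a pure change contrast, and a shift that vanishes by follow-up. Knowledge of the arm continues in an open-label trial, and whatever persists cancels in a change contrast.
- *Women who withdraw before treatment never give a baseline.* Some may have completed the kit in the final month. Such women are in any case substituted under the Randomization section, which is a separate matter.

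**Conclusion.** The point holds in limited form. The documents show that the only baseline is open to influence by allocation. They do not show that such a shift occurs, or how large it would be. If it occurs, it passes in full into a change contrast or a treatment-by-time effect measured from the first kit, and in proportion ρ into a baseline-adjusted contrast. Changes used for the cost-utility analysis are exposed in the same way.

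For a 3-point shift confined to baseline, the false-positive rate of a change contrast is about 17-37%, under assumed SD 20-25, correlation 0.5-0.7 and 140 per arm. The direction of the effect does not depend on those inputs; the size does.

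The affected endpoints are secondary, and the protocol treats them as supportive and exploratory. Severity is minor to moderate.

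**What to change.** Add one electronic kit (EHP-30, NRS, EQ-5D) at consent, to be completed before randomisation, in the existing Baseline column of the Schedule of Events. Name it as the baseline reference in the mixed models and in the QALY calculation. Keep the present kit, within one month of first treatment, as a separate pre-treatment assessment, so that the equal-lead-time reading is preserved. Amend Points of Assessment and Procedure to match.

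The cost is one extra questionnaire per woman, with slight added burden, and a line in the schedule. Questionnaires are already sent from REDCap, and consent already precedes randomisation. For any women randomised before the change no pre-allocation reading can be recovered; for them, between-arm levels at follow-up are the contrasts to rely on. The extra kit does not remove open-label influence on the follow-up answers themselves. It only restores a reference that allocation cannot have touched.
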